| 11. Evaluation and consideration of the forseeable risks and disadvantages to the the study participants in contrast to the expected benefit for them and future patients.  Risk-benefit evaluation) | The risks of using the oesophageal Doppler probe are seen as minimal. According to Deltex Medical the probe has thus far been used approximately 800,000 times and there has only once been a suspicion of an oesophageal injury. Previous studies have no indication of Doppler-associated complications. By avoiding nasal insertion of the probe one avoids the risk of epistaxis and for the purposes of this study oral insertion of the probe will be used.  Against these minimal risks stand the findings of previous studies using the oesophageal Doppler which have demonstrated a reduced rate of complications as well as a reduced length of ICU and hospital stay.  For the use of the LiDCOrapid there is no additionally risk for the study patients as the monitor derives the signal of the invasive arterial pressure measurement and calculates by algorithms the puls-power of the heart beats from the arterial blood pressure curve and determines consecutively stroke volume. Given that every patient gets an arterial line placed due to the kind of operation there is no additionally risk.  The development and the evaluation in the clinical context of a haemodynamic algorithm for liver resections on the basis of minimal-invasive monitoring is in due proportion to the risks of the participating patients. |
| a. Expected therapeutic benefit for the study participants (individual benefit for a single patient) | It has been shown in other patient populations that patients with improved haemodynamics suffered a lower rate of complications and had an earlier stabilisation of their clinical condition, thereby allowing them earlier to be discharged home.  This proven effect in other populations is also the benefit expected to be seen in the protocol guided groups of this trial. |
| b. Predicted future medical uses for patients (**Group benefit)** | It has to be the aim of this study to examine the influence of advanced haemodynamic monitoring and the use of clinical therapy protocols based on clinical studies to lower the rate of complications.  Given that this kind of surgery is common (approximately 250 interventions per year in the Department of General, Visceral and Transplantation sSurgery, Charité – University Medicine Berlin, Campus Virchow Clinic) and it is associated with a high rate of postoperative complications, the benefit of new knowledge is of high value for future patients to perform this intervention with a lower rate of complications. |
| c. Risks and discomfort for the study participants (list each seperately) | The risks of the oesophageal Doppler are injury to the oesophagus and bleeding in the nasopharyngeal cavity. The danger of an oesophageal injury can be classified as small given that, according to Deltex Medical, there has only been one case of a possible oesophageal injury in over 800,000 uses of the probe.  The danger of bleeding in the nasopharyngeal cavity is higher with nasal insertion of the probe. However as the probe will be inserted orally in this study then this risk can also be said to be small. Furthermore none of the previous studies attributed any relevant morbidity to the oesophageal probe.  Similarly the level of discomfort caused to patients is likely to be small. A nasogastric tube is comparable to a Doppler probe in size and shape. Positioning of nasogastric tubes is even tolerated well by awake patients using local anaesthesia. However in this study the oesophageal probe will be placed following induction of anaesthesia and removed again before extubation. Therefore the level of discomfort can be classified as minimum.  For the patients of the LiDCO group there is no additionally risk because the patients get an arterial line placed due to the kind of surgery. The signal of the arterial line will only be additionally analysed to determine the haemodynamic parameter.  The intended blood withdrawals will be performed in the same manner as the blood withdrawals due to the clinical routine. Generally by taking the blood samples there is no interference with the physical well-being. In isolated cases harmless disturbances of the circulation can occur that can be avoided substantially by taking a short-term rest after the blood withdrawals. At the point of puncture haematoma can occur. On rare occasions  At the site of the puncture the patient can get an hematoma. In rare cases injury of the blood vessels (veins and arteries) and nerves as well as inflammation of the site of the puncture can occur. A transmission of infectious diseases is not possible due to the use of sterile disposable systems and cannulas are used to withdraw blood probes. Additionally the trained staff aims to use intravenous lines to withdraw the blood probes. The amount of blood withdrawn will be approximately 20-30 ml per day during the five postoperative days. |
| 12. Risk control measures | The dangers of placing the oesophageal probe comprise oesophageal injury and nasopharyngeal bleeding. For this reason pre-existing pathology or recent operations in the area of the oesophagus or nasopharyngeal cavity represent risk factors for these complications and should be regarded as contraindications to study participation.  The siting of the oesophageal probe takes place under the strict supervision of an anaesthetist and all patients will be monitored post-operatively until their discharge or for 30 days. |
| 13. Study termination criteria | Under the following conditions premature separating of a patient from the study occurs in accordance with the abort criteria:  The following events can be regarded as reasons for termination:  • personal wish of the patient  • every other situation, where in the opinion of the study physician, further participation in the trial would not be in the best interests of the patient  • unblinding in the case of a medical emergency  • significant protocol breaches  • Subsequent occurrence of an exclusion criterion  A premature cessation of the study and/or an abandonment of the entire study can occur in the following circumstances:  • Decision of the study leader where untenable risks exist according to risk-benefit analysis  • new (scientific) developments during the course of the study demonstrating a risk to participants by further continuation of the study (a positive risk-benefit ratio is no longer applicable) |
| 14. Number, age and sex of participants | There are no studies in the literature for the primary and secondary endpoint that show reliable data to enable a statistical calculation of the number of patients that would be needed.  Therefore this study is planed as a pilot study including 20 patients per group that means overall 60 patients are included. In this study no gender-based selection of the study patients will be performed. Man and woman aging more than 18 years are included in the study. |
| 15. Description of statistical methods and biometric basis for required number of cases with signature of statistician | For all endpoints of the study explorative data analyses will be performed and descriptively analysed. Because of the small sample sizes and possible outliers and/or skew distributions, the primary and secondary endpoints will be analysed using non-parametric statistical tests (qualitative data: Fisher’s exact test, quantitative data: Mann-Whitney-U test for independent groups or Wilcoxon-test for paired observations).  All test will be performed with an alpha error = 5% (two-sided). The calculated p values will be considered as explorative and do not allow confirmative generalization. Due to the same reason we do not perform alpha adjustment for multiple testing.  As we can not perform a calculation of the sample size the number of patients to be included in this study follows objective considerations and the clinical possibilities to perform the conductance of this pilot study. With the results of this study a consecutive prospective randomized study with calculation of the sample size shall be initiated.  The analysis of the study results will be performed according to the “intention-to-treat” as well as to the “per-protocol” principle.  The numerical calculations are performed with the statistical program SPSS, Version 17, Copyright SPSS, Inc., Chicago, Illinois 60606, USA. |
| 16.  a. Statement of exclusion criteria, with explanation if necessary | **Inclusion criteria:**   - Written informed consent from patient - Patients undergoing elective liver resection in Charité - University Medicine Berlin, Campus Virchow-Clinic   **Exclusion criteria:**   - Aged less than 18 years - No written informed consent from patient - For female patients: pregnancy or lactation - Inability to communicate freely in the German language - Lack of willingness to safe and hand out pseudonymised data within the clinical study - Simultaneous participation of the patient in another study - Accommodation in an institution due to an official or judicial order - Members of staff of the Charité - Unclear history of alcohol used disorder - Advanced disease of the oesophagus of nasopharyngeal cavity - Operations in the area of the oesophagus or nasopharynx within the last two months - History of bleeding tendency e.g. Von Willebrands disease - Neurological or psychiatric disease - Chronic heart failure New York Heart Association (NYHA) class IV - American Society of Anaesthesiologists (ASA) classification greater than IV - Chronic renal failure with dependency of haemodialysis - Existence of a pulmonary oedema in the pre-operative chest x-ray - History of intracranial haemorrhage within one year - Allergy to gelatin |
| 16.  b. **Participant information** *(who gives this statement verbally and indicates how much time remains between declaration and consent, otherwise by reference to their contents in an appendix* | see appendix |
| c. **Declaration of consent** *(reference to their contents in an appendix is possible)* | see appendix |
| d. If necessary **obtain information and consent from legal representatives** *( also if required describe the procedure to obtain a judicial review)* | Not applicable |
| 17. Methods to recruit study participants (notices, newspaper advertisements, etc) | All patients undergoing abdominal surgery in the Charite Campus Virchow will be screened to see if they fulfil the inclusion criteria. |
| 18. If necessary: **Reason for inclusion and justification of therapeutic use in individuals who are under-age and/or are incapable of giving consent** | Not applicable. |
| 19. Relationship between the study participants and the research physician (is the treating physician also the research physician?) | The patients will form part of the daily treatment routine within the departments of General, Visceral and Transplantation Surgery and Anaesthesiology and Intensive Care in the Charite Campus Virchow clinic. The study physicians themselves will also be recruited from these same departments. Both departments have extensive experience with clinical studies.  Patients can decide freely whether or not to enter the study and their decision on whether or not to participate will not have an influence on their quality of care.  The study staffs are not the treating doctors. |
| 20. If applicable: Ifinclusion of dependant individuals is possible the research physician, or sponsor, must give an explanation | Not applicable. |
| 21. Outline measures which allow study participants to make a statement on whether they’re participating simultaneously in other studies or before the expiry of a period specified in earlier studies | At the time of the entry assessment the study participant will be asked if he/she is participating in a parallel study. If he/she is participating in another study, or has participated in another study within the past week before inclusion, then he/she cannot participate according to the exclusion criteria set for this study. |
| 22. If applicable: Remuneration and/or reimbursement of costs of study participants (amount, specify expenses paid) | Not applicable. |
| 23. If applicable: Plan for further care and medical support of the affected individuals after termination of the study | The study duration is limited from the beginning of surgery up to the first postoperative day. After the operation a monitoring period follows until hospital discharge or until day 8 postoperatively whichever is earlier. The postoperative care of the patient is ensured as the patient will only be discharged from the hospital after fulfilment of the discharge criteria. That offers post-trial coverage to aim for avoidance that the patient does suffer unrecognized complications.  The study will be unblended after the last visit of the last patient. |
| 24. If applicable: Insurance of the study participants (insurance confirmation and conditions of insurance, insurer, coverage, duration of insurance) | The ethical application, the participant information and the declaration of consent were sent by email to Ms. [name] to receive the confirmation of the hospital insurance for this study. |
| 25. If applicable: Documentation procedure (reference to the CRF-**records** if possible) | The data acquisition will be accomplished by means of an paper-based case report form.  The data will be saved under a pseudonym. The study personal generates for every newly registered patient a pseudonym according to the below described guidelines. The categorical allocation of each patient is kept on a paper record which must be stored securely.  The pseudonym will be generated from the first two letters of the study name, the number of the center CVK=1, CCM=2, and a three digits incrementally increasing number.  As an example for the first study patient:  LE 1 001 |
| 26. If applicable: A description of the state of health of any healthy individuals concerned must be documented | Patient inclusion occurs by virtue of their having disease that indicates a liver resection. No healthy patients will be included in this study. |
| 27. If applicable: Methods to detect, document and communicate adverse events (when, with whom and how??) | The patients will be supervised intensively during the operation by the anaesthetist and can only leave the operation area when the discharge criteria are fulfilled in the recovery room.  Apart from the routine daily care delivered by the physicians in the departments of General, Visceral and Transplantation Surgery, there will also be a visit from the study physicians of the Anaesthesiology department, so that adverse events can be detected.  The occurrence of adverse events should be communicated to the study director within 24 hours.  A liver resection represents a surgical intervention with increased risk and deviation of parameter frequently occurs. Due to that fact a list of exceptions will be generated because the deviations of the values are related to the surgical intervention and are not indicative of an adverse event induced by the study protocol. For the values of perioperative blood samples a plausibility list will be generated which regulates the limits the pathological values from the reportable events.  Post-operative monitoring will continue until the day of hospital discharge or the 8th post-operative day, whichever is earlier. |
| 28. Procedures to ensure the secrecy of stored data, documents and, if applicable, samples. State how the encoding of patient data occurs *(please don’t use patient initials and birthdays as coding schemes!)* | A pseudonym is generated for every patient and the list of pseudonyms is kept locked away. Patient documentation is only done using the pseudonym.  The pseudonym will be formed from the first two letters of the study name followed by the number of the center CVK=1, CCM=2, followed by a three digits incrementally rising number.  As an example for the first patient of the study:  LE 1 001 |

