| 4.Subject of the study and its aims  (Hypothesis divided into primary and secondary hypotheses) | Primary Hypothesis:  Compared to conventional therapy an intra-operative goal-directed haemodynamic management by monitoring with LiDCOrapid or oesophageal Doppler improves haemodynamics measured by stroke volume (SV) in patients undergoing elective liver resection.  Secondary hypothesis 1:  Compared to conventional therapy an intra-operative goal-directed haemodynamic management by monitoring with LiDCOrapid or oesophageal Doppler reduces the incidence of perioperative dysfunction (cerebral, pulmonary, renal, abdominal and cardiovascular), the amount of intraoperative blood loss and the postoperative incidence of infections and quality of life in patients undergoing elective liver resection.  Secondary hypothesis 2:  Compared to conventional therapy an intra-operative goal-directed haemodynamic management by monitoring with LiDCOrapid or oesophageal Doppler the postoperative liver function in patients undergoing elective liver resection.  Study groups:  The administration of the volume and catecholamine therapy is carried out by:  1.) Conventional standard therapy  2.) Goal-directed haemodynamic management by monitoring with oesophageal Doppler  3.) Goal-directed haemodynamic management by monitoring with LiDCOrapid  Primary outcome measure:  Stroke volume before intra-operative start of liver resection  Secondary outcome measures:   - Intra-operative and post-operative haemodynamic parameters - Intra-operative and post-operative blood loss - frequency of organ dysfunctions (cerebral, pulmonal, renal, abdominal, cardiovascular) - Post-operative liver function (LiMAx-test, ICG-Clearance, liver Doppler, laboratory tests: enzymatic and chemical parameters) - Peri-operative weight change - Post-operative incidence of infections - Satisfaction of the patients, the surgeons and anaesthetists - Time to fulfilling discharge criteria - Length of intensive care stay and hospital stay (LOS) - Quality of life measure (EQ-5D) - Laboratory tests: peri-operative endothelial and immunological alterations |

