**Wound infection:**

**Superficial post-operative wound infection:**

Infection at the incision site within 30 days of operation which only involves the skin or subcutaneous tissues,

and one of the following criteria are met:

- Purulent discharge from the superficial incision
- Microbe isolated from culture of an aseptically obtained wound secretion or a tissue culture of the superficial incision

and one of the following signs:

- Pain
- Tenderness
- localised swelling
- Erythema or warmth
- The surgeon would open the superficial incision except that a **negative culture exists before the diagnostic decision**.

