**Deep post-operative wound infection:**

Infection within 30 days of operation. The infection appears to be associated with the operation and involves muscle tissue and fascial layers.

In addition to this one of the following criteria must be met:

- Purulent secretions from deep in the incision but not from an organ and/or body cavity
- Spontaneous drainage or deliberate surgical incision when the patient has at least one of the following symptoms:
- Fever (>38°C)
  - localised pain or tenderness
  - culture is confirmed negative
- An abscess or other sign of infection is evident from clinical, radiological or histopathological examinations or during re-operation
- diagnosis made by the surgeon

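### The protocol gives two incompatible ends to post-operative monitoring, and under either discharge-limited reading the infection count depends on length of stay

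*Protocol*

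**What the plan says.** Three items of the protocol state when post-operative monitoring ends:

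- Item 12 (risk control): "all patients will be monitored post-operatively until their discharge or for 30 days".
- Item 23 (care after termination): "After the operation a monitoring period follows until hospital discharge or until day 8 postoperatively whichever is earlier".
- Item 27 (adverse events): "Post-operative monitoring will continue until the day of hospital discharge or the 8th post-operative day, whichever is earlier".

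Appendix 4 sets the time limit for wound infection. The superficial form is "Infection at the incision site within 30 days of operation which only involves the skin or subcutaneous tissues". The deep form begins "Infection within 30 days of operation. The infection appears to be associated with the operation and involves muscle tissue and fascial layers". The other infections in that appendix carry no 30-day limit.

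Secondary hypothesis 1 in item 4 names the "postoperative incidence of infections", and the list of secondary outcomes includes it without a time window. The list also contains time to fulfilling discharge criteria, ICU and hospital stay, organ dysfunction and EQ-5D. Item 10 has EQ-5D repeated at the end of the study and gives no day. No item describes contact with patients after discharge.

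**The concern.** Two problems follow.

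First, site staff cannot tell which rule to apply. Items 23 and 27 stop at day 8 at the latest. Item 12 allows up to 30 days and does not say whether the earlier or the later limit governs.

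Second, where monitoring ends at discharge, the time a patient is at risk of being counted as infected depends on another outcome, length of stay. The protocol expects the guided arms to go home earlier (item 11a), and its own table of oesophageal Doppler studies lists reductions in hospital care of 13% to 39% (Appendix 1). An arm that leaves sooner is watched for less time, so the error favours the intervention.

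At stake are the infection comparison and the infection rate itself. Item 15 says this pilot is to lead to a randomised study with a calculated sample size. A rate taken from a short, discharge-dependent window would be a poor input to that calculation.

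**Working it through.** **The plan's own figures.** The only related figure that can be reproduced is the sample size, 3 × 20 = 60, and the point does not depend on it. The protocol gives no length of stay, infection rate or time to infection.

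**The windows side by side.** Let L be the day of discharge.

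| Source | Infections can be seen until | Depends on stay? |
|---|---|---|
| Items 23 and 27 | min(L, 8) | Yes, for L < 8 |
| Item 12, earlier limit governs | min(L, 30) | Yes, for L < 30 |
| Item 12, 30 days for everyone | 30 | No |
| Appendix 4, wound infection | 30 (definition) | No |

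Day 8 covers at most 8/30 = 27% of the period over which a wound infection qualifies, leaving 22 days outside it. Only the third reading agrees with Appendix 4, and it contradicts items 23 and 27.

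**Illustration of size.** All inputs here are assumptions:
- true infection risk of 20% in both arms;
- time to onset gamma with shape 2.5 and scale 4 days (median 8.7 days), with distribution function F;
- log-normal stay with log-SD 0.4.

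Counted rate = 0.20 × E[F(min(L, c))], with c = 8 or 30. For a patient who stays 8 days or more under the day-8 rule, F(8) = 0.45, so the counted rate is 0.20 × 0.45 = 9.0%. Averaging over stay gives:

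| Median stays (days) | Counted, c = 8 | Spurious reduction | Counted, c = 30 | Spurious reduction |
|---|---|---|---|---|
| 14 v 10 | 8.9% v 8.3% | 6% | 14.9% v 11.6% | 22% |
| 10 v 8 | 8.3% v 7.5% | 10% | 11.6% v 9.3% | 20% |
| 10 v 6 | 8.3% v 6.0% | 28% | 11.6% v 6.6% | 43% |

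Reductions are taken before rounding the rates. With log-SD 0.5 the c = 8 reductions are 8%, 10% and 27%. At c = 8 the share of infections counted is about 44%, 41%, 37% and 30% for median stays of 14, 10, 8 and 6 days.

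**Second onset model.** Take F(t) = (1 − 0.5^(t/m)) / (1 − 0.5^(30/m)). With m = 10, F(8) = 0.486 and F(5) = 0.335. If one arm all leaves on day 5 and the other stays to day 8 or later, the counted rates are 0.20 × 0.335 = 6.7% and 0.20 × 0.486 = 9.7%, a ratio of 0.69. For m = 7 and m = 14 the ratios are 0.71 and 0.67. The direction is the same, and the size is near the largest c = 8 case above.

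**In patients.** At 10 v 6 days with c = 8, 20 × 0.083 = 1.7 against 20 × 0.060 = 1.2, a difference of about half a patient per arm.

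**The case against.** **The 30 days is a case definition.** Appendix 4 says what qualifies as a surgical wound infection and is not a visit schedule. A day-6 infection satisfies it, and the other infections carry no such limit. This stands: the mismatch with 30 days concerns wound infection only. The dependence on discharge, however, applies to any infection counted under these rules.

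**The bias may be small.** When most stays exceed 8 days, the day-8 rule is close to a fixed window. The 10 v 6 case is a 40% shorter stay, just above the 13% to 39% range in Appendix 1, whereas 10 v 8 (20%) and 14 v 10 (29%) lie within it. With 20 patients per arm, Fisher's test could not register half a patient. This stands as a limit on size. The bias would still sit in the rates carried forward to the next study.

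**Long stays.** A reader might infer that every stay over 8 days is truncated. The protocol does not say so. Day 8 limits monitoring, the stay outcomes are listed without a cap, and a discharge date can come from the hospital record. If recording did stop at day 8, simulated Mann-Whitney power for 14 v 10 days (log-SD 0.5, 20 per arm) would fall from about 52% to about 31%. If discharge dates are recorded, nothing is lost. Nor do the two harms peak together: long stays make the infection bias small, and short stays leave little to truncate.

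**Day 1.** A reader might also count "The study duration is limited from the beginning of surgery up to the first postoperative day" as a third rival window. The next sentence of item 23 adds the monitoring period, so it is not one.

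**Conclusion.** The contradiction between item 12 and items 23 and 27 is on the page and needs no outside data. So is the lack of any described ascertainment after discharge for an infection defined over 30 days. Followed as written, items 23 and 27 count infections only to the earlier of discharge and day 8, which can favour an arm discharged earlier. Adopting item 12 as the earlier of discharge and 30 days would make the dependence stronger.

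The size cannot be known from the protocol. Under the assumed 20% risk and gamma onset, the day-8 rule produces a spurious relative reduction of about 6% to 28%, depending on the stays assumed. The effect needs stays under 8 days that differ between arms.

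The protocol does not support the stronger conclusion that hospital stay is lost beyond day 8. The primary outcome, stroke volume before the resection starts, is untouched, and item 15 treats all p values as exploratory. Severity is moderate: correct it, chiefly because the pilot is meant to inform a later sample-size calculation.

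**What to change.** 1. State one post-operative follow-up period, in the same terms, in items 12, 23 and 27, and say which limit governs.
2. Count infections over one fixed window for every patient, whatever the discharge date. If the 30-day definition is kept, ascertain to day 30 by record check or telephone. Otherwise use one shorter common window, still completed for patients discharged earlier, and label the outcome with it.
3. State that hospital stay, ICU stay and time to discharge criteria are recorded to actual discharge. One sentence settles the truncation question.
4. Fix the post-operative day of the final EQ-5D.

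The cost is a short amendment and one brief contact or record check for each of 60 patients. Discharge dates can come from routine records. The treatment protocol, the primary outcome and the sample size do not change.
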